**Figure 2 figure2:**
[figure not shown]
Screenshots of the Good Start Matters mHealth (mobile health) Parenting Program focused on feeding practices.

**Figure 3 figure3:**
[figure not shown]
Screenshots of the Good Start Matters mHealth (mobile health) Parenting Program focused on physical activity.

##### Module 0: Welcome

This introductory module will offer a general overview of the app’s functionality and features, outline the content to be covered, and provide access to reliable information sources and external services for more specialized needs.

##### Module 1: Get Ready to Make Changes

This module will introduce parents to foundational concepts, goals, and expectations for young children. Recommendations will be related to healthy eating, active play, and screen time based on the Canadian Food Guide [55] and the Canadian 24-hour Movement Guidelines [56]. This module will also highlight the importance of developing fundamental movement skills such as balancing, locomotion, and coordination to support engagement in more complex physical activities later in life [57,58]. Using self-assessment tools integrated into the app, parents will evaluate their child’s current health habits, identify areas for improvement, and set goals.

Examples of BCTs [54] included in this module are as follows:

Shaping knowledge: Structure of a healthy plate; screen time, and active play guidelines; what are fundamental movement skills (balancing, locomotion, and coordination).Natural consequences: Benefits of promoting healthy eating, active habits, and fundamental movement skills.Comparison of outcomes: Citing Canada’s Food Guide [55], and 24-hour Movement Guidelines [56] as credible sources.Monitoring and feedback: Evaluation of the extent to which the child meets health behavior guidelines.Goals and planning: To serve a healthy plate and facilitate active play.Rewards and threats: Encouragement to use reward charts with the child.

##### Module 2: Divide Responsibilities

This module will focus on the division of responsibilities in dietary and activity contexts, drawing from Ellyn’s approach [59,60]. Parents will learn to differentiate between their role in providing healthy options and their child’s role in making decisions from the healthy options offered (“the parent provides, the child decides”). Practical examples will demonstrate how to implement this approach in real-life situations, while challenge questions will help parents anticipate and apply strategies in daily life. Self-assessment tools will encourage reflection on how well parents currently provide healthy opportunities for their child to make age-appropriate decisions, and recommended goals will emphasize both exposure to healthy options and child decision-making.

Examples of BCTs [54] included in this module are as follows:

Shaping knowledge: Division of Responsibilities in eating and activity; exposure to healthy foods; facilitation and support for active play; reducing pressure and forceful practices.Natural consequences: Benefits of providing options within boundaries and encouraging age-appropriate decisions.Generalization of target behavior: Division of responsibility concept initially taught in the nutrition context and then extended to active play situations.Comparison of outcomes: Citing Ellyn’s Division of Responsibility approach as a credible source [59,60].Monitoring and feedback: Evaluation of the extent to which the parent provides healthy opportunities and challenge scenarios on how to deal with a picky eater.Goals and planning: To serve 2+ veggies at dinner; engage in suggested fundamental movement skills activities; or take children to places to be active.Rewards and threats: Evaluative feedback to parents after completing self-monitoring tools and challenge questions.Self-belief: Encouragement of gentle parental persuasion to promote child engagement in healthy behaviors.

##### Module 3: Provide Opportunities

Centered on stimulus control [61,62], this module will emphasize the role of parents in modifying the home environment to promote healthy habits, such as managing food accessibility, removing screens from bedrooms, rotating active play equipment, and offering opportunities for both organized and unstructured physical activities. Parents will critically examine their home environment to identify and modify unhealthy stimuli, aiming to “make the healthy option the easy choice.” Self-assessment tools will evaluate how well the home environment supports healthy behaviors, challenge questions will address common barriers, and recommended goals will focus on increasing the availability of healthy options at home.

Examples of BCTs [54] included in this module are as follows:

Shaping knowledge: Controlling stimulus and environmental antecedents of unhealthy habits at home, exposure/availability of healthy foods, and facilitation of active play.Natural consequences: Benefits of exposure to healthy environments.Antecedents: Adding objects and modifying the home environment to facilitate adoption of healthier behaviors.Generalization of target behavior: Stimulus control and repeated exposure concepts initially taught in the nutrition context and then extended to active play.Monitoring and feedback: reflection on what the child’s home environment stimulates and a scenario on how to deal with a child rejecting a specific sport class.Goals and planning: To cook healthy plate meals; plan healthy snacks ahead of time; rotate active play toys; or look for sport/dance classes.Rewards and threats: Evaluative feedback to parents after completing self-monitoring tools and challenge questions.Social support: Encouragement of parental practical, emotional, and unspecified support for children to engage in healthy behaviors.Associations: Prompts/cues in the environment to influence parent and child behaviors; remove rewarding stimulus at home.

##### Module 4: Engage Your Family

This module will highlight the role of family interactions in fostering healthy lifestyle behaviors. Parents will learn to model healthy habits, such as eating nutritious meals and staying active, and to establish family routines that support positive modeling. It will emphasize the importance of family meals and shared activities, providing practical tips for making these experiences enjoyable. Self-assessments will evaluate current family routines and modeling behaviors, while recommended goals will focus on family-centered activities like regular family meals and fun active games together.

Examples of BCTs [54] included in this module are as follows:

Shaping knowledge: How to establish family-centered routines and create opportunities for modeling family-based interactions.Natural consequences: Benefits of family-based activities and positive/healthy role modeling.Antecedents: Advice to maximize quality family time, modeling, and positive experiences.Generalization of target behavior: Healthy plate concept initially focused on child meals, further extended to the whole family; focus on creating regular family meals and active time.Monitoring and feedback: Evaluation of current family activities and the extent to which parents model healthy habits.Goals and planning: To coparticipate in active play; eat a healthy plate in front of the child; or have family meals.Rewards and threats: Evaluative feedback to parents after completing self-monitoring tools and challenge questions.Identity: Framing parents as key role models.Social support: Promotion of parental support (practical, emotional, and unspecified) to engage children in healthy behaviors.Self-belief: Encouragement of gentle parental persuasion to promote child engagement in healthy behaviors.Associations: Ensuring fun/enjoyable games are part of family physical activities and mealtimes.

##### Module 5: Create Routines

This module will emphasize the importance of structure and boundaries in fostering healthy routines. Parents will learn to establish consistent mealtimes, manage screen time, and create predictable schedules that support healthy habits. The module will highlight the need to place limits on less healthy behaviors, such as unhealthy food intake and excessive screen time, while encouraging active play without unnecessary restrictions to support the development of fundamental movement skills. Practical tips will include creating screen-free zones, setting rules around sugary treats, promoting outdoor exploration, and prioritizing family-centered activities. Self-assessments will help parents evaluate their current boundaries, and recommended goals will include pairing limits with education to encourage outdoor play and consistent meal routines.

Examples of BCTs [54] included in this module are as follows:

Shaping knowledge: Creating routines, setting boundaries and limits in foods and screen time, and rethinking risky play boundaries.Natural consequences: Benefits of predictable environments; eating without distractions; consequences of highly processed foods intake, and risky play restrictions.Repetition and substitution: Focus on creating regular family meals and active time; replacing screen time during meals with fun-fact activities.Monitoring and feedback: Evaluation of the extent to which parents have boundaries and regular routines at home.Goals and planning: To eat meals and snacks at regular times; limit treats and sugary drinks or screen time; or let the child explore their limits at the playground.Rewards and threats: Evaluative feedback to parents after completing self-monitoring tools and challenge questions.

##### Module 6: Give Positive Feedback

Based on operant conditioning principles [63] (“behaviors depend on their consequences”), this module will teach parents how to respond to their child’s actions. Practical tips and examples will demonstrate how to use differential attention to reinforce only healthy behaviors with effective feedback methods [61,62], including verbal praise, nonfood/nonscreen rewards, physical gestures, and second- or third-hand compliments engaging multiple caregivers. Self-assessments will help parents reflect on whether they are reinforcing healthy behaviors or unintentionally encouraging negative ones, challenge questions will provide practice scenarios (eg, managing food-related tantrums), and recommended goals will emphasize using some of the feedback techniques provided.

Examples of BCTs [54] included in this module are as follows:

Shaping knowledge: How to respond to child health behaviors to increase/decrease the likelihood of occurrence; how to deal with tantrums.Natural consequences: Consequences of different types of parental immediate responses to child behaviors (ie, reinforcing, punishing, or ignoring).Monitoring and feedback: Evaluation of the extent to which parents reinforce healthy or unhealthy child behaviors.Goals and planning: To provide positive feedback after healthy eating or small rewards for active behaviors, or use second-hand praising techniques.Rewards and threats: Evaluative feedback to parents via self-monitoring tools and challenge questions; encouragement of incentives and reward systems for children based both on effort and outcomes.Social support: Encouragement of parental practical, emotional, and unspecified support for children to engage in healthy behaviors.Self-belief: Encouragement of gentle parental persuasion to promote the child’s active role and engagement in healthy behaviors.Associations: Removing rewards for unhealthy behaviors.

##### Module 7: Involve Your Child

This module will focus on providing guidance and education on how to involve children in age-appropriate decision-making to promote psychological autonomy. Parents will learn strategies such as involving their child in simple meal preparation tasks (eg, washing vegetables, arranging ingredients) and teaching physical skills (eg, biking, kicking a ball) paired with gentle encouragement to help children understand the benefits of healthy choices, read their body signals, and feel motivated to participate in physical activities without pressure. Self-assessment tools will help parents reflect on how much autonomy their child currently has, and recommended goals will focus on empowering children to make simple decisions within a range of only healthy options.

Examples of BCTs [54] included in this module are as follows:

Shaping knowledge: How to promote children’s autonomy and skills to make healthy choices as they grow through age-appropriate decisions, education, and guidance.Natural consequences: Benefits of supporting the child’s decision-making process within boundaries.Generalization of target behavior: Child involvement in simple tasks and decision-making was first presented in the nutrition context and then extended to the activity context.Monitoring and feedback: Evaluation of the extent to which the child can decide on their own activity and eating habits within boundaries.Goals and planning: To respect children’s satiety cues; involve them in simple meal preparation; or ask about preferred physical activities to try.Rewards and threats: Evaluative feedback to parents via self-monitoring tools and challenge questions.Social support: Encouragement of parental support (practical, emotional, and unspecified) to engage children in healthy behaviors.Self-belief: Encouragement of parental persuasion to promote the child’s active role and engagement in healthy behaviors.

##### Module 8: Work as a Team

This module will address the importance of positive coparenting practices to strengthen the coparenting subsystem and create a consistent and supportive environment. Parents will be encouraged to collaborate with other key caregivers to agree on goals, expectations, and practices, facilitated by effective communication and cooperative decision-making tips. Self-assessment tools will evaluate alignment in coparenting practices, and recommended goals will emphasize partnership and collaboration in child-rearing tasks related to lifestyle habits.

Examples of BCTs [54] included in this module are as follows:

Shaping knowledge: How to engage in positive coparenting practices; effective communication; cooperative and consistent practices around child lifestyle habits.Natural consequences: Consequences of disagreements and conflicts in front of the child; inconsistent approaches and lack of structure.Monitoring and feedback: Evaluation of the extent to which coparents’ expectations, goals, and practices about the child’s behaviors align.Goals and planning: To discuss goals and expectations for the child and approaches to meet these goals; praise the coparent for using practices they have agreed on; or provide structure at home.Rewards and threats: Evaluative feedback to parents via self-monitoring tools and challenge questions; promotion of social reward to coparent for engaging in an agreed-on parenting practice.Social support: Coparents are encouraged to seek help from and support each other to engage in positive parenting practices.

##### Module 9: Recap and Commit

The final module will summarize the program’s content and key takeaways. It will encourage parents to reflect on the things they have accomplished, the resources and skills they can use, and commit to continue using health-promoting parenting and coparenting practices.

Examples of BCTs [54] included in this module the following:

Shaping knowledge: Recap on health behavior guidelines regarding nutrition, active play, and screen time; recommended autonomy-promoting and structured practices; division of responsibility in nutrition and activity; importance of family-centered activities, and joint family management.Monitoring and feedback: Review of progress made; existing strengths, resources, and skills to continue using positive parenting and coparenting practices.Goals and planning: Parents asked to make statements and commitments to maintain existing or use new positive parenting and coparenting practices.Identity: Framing parents and caregivers as key role models.Social support: Encouragement of parental social support for children to engage in healthy behaviors.Self-belief: Focus on previous successes in using positive parenting and coparenting practices.

### Measures

#### Overview

Data collection will occur at baseline and follow-up (approximately 2 months after randomization) for all variables listed below except for sociodemographic variables, which will be evaluated only at baseline. Participants will complete all surveys online using REDCap.

#### Primary Outcomes

Parenting practices related to nutrition and activity will be measured with items modeled after the validated food [64] and physical activity [65] parenting item banks designed for 5- to 12-year-olds, with some questions adapted for younger children (eg, the original item asks “how often do you have your child help prepare dinner meals”), while the adapted item will ask “how often do you involve your child in simple food tasks when preparing meals (eg, help wash vegetables, arrange the vegetables). Both item banks were informed by parenting and obesity experts and have been evaluated for construct validity (ie, designed to capture the 3 parenting domains of control, structure, and autonomy promotion) related to nutrition and active play. These item banks have shown strong psychometric properties, including measurement invariance by parent gender, making the comparisons valid between mothers and fathers, and Cronbach α ranging from 0.67 to 0.96 [64-67]. Additional items on food, physical activity, and media parenting practices were developed for this study to align with the intervention content. Accordingly, we will assess and report on the psychometric properties of the parenting measurement tools used in this RCT, focusing on construct validity (via factor analysis) and reliability (via Cronbach α). Reassessing these properties in the final sample will provide a more accurate evaluation of the validity and reliability of the measures applied in this trial.

Coparenting practices will be evaluated with items adapted from the Agreement subscale of the Coparenting Relationship Scale [17], designed for children aged 6 months to 3 years and further used with children up to 7 years old [18,68]. The scale shows adequate psychometric properties, including construct validity and reliability (Cronbach α ranging from 0.67 to 0.74). The questions will inquire about the level of agreement between key caregivers regarding their expectations, goals, approaches, and conceptions about their child’s lifestyle behaviors. Additionally, coparenting practices will be examined in 2-parent families by comparing the parenting practice scores of both parents/caregivers within the family.

#### Secondary Outcomes

Child eating behaviors will be evaluated with the Child Eating Behavior Questionnaire [69], examining child emotional overeating, food responsiveness, food fussiness, and satiety responsiveness. This instrument, designed for children aged 2-9 years, has been extensively used, showing adequate psychometric properties, including Cronbach α ranging from 0.72 to 0.91 [69]. In addition, parents will be asked to report on the number of days per week that their child consumes key food markers (ie, fruit and vegetables, fruit juice and sugary drinks, sweet and salty treats), with questions adapted from the Canadian Community Health Survey [70] and the Center for Diseases Control’s Behavioral Risk Factor Surveillance System Questionnaire [71] and National Youth Physical Activity and Nutrition Study [72].

Child active and outdoor play will be measured with questions from the instrument designed by Burdette et al [73] for young children. The questions inquire about the number of minutes per day and the number of days per week that the child engages in active and outdoor play on a regular weekday and weekend day.

Children’s screen time will be measured by inquiring about the number of days in the previous week that children spent more than 1 hour/day in front of screens, when counting all screen-media devices (eg, TV, computer, tablet, and smartphone).

#### Covariates

Covariates will include child-level, parent-level, and family-level variables that may have an influence on family dynamics, parenting practices, and child health behaviors. Sociodemographic questions (some created for this study and others adapted from the Canadian Community Health Survey [70] and General Social Survey [74]), will cover child and parent age and sex, parent gender, marital status, education, employment status, cultural/ethnic background, household income, number of households where the child lives in, number of children living at home and their age group, number and type of family members in the household, and familial relationship between participating coparents. In addition, we will evaluate the division of responsibilities between key caregivers regarding child-rearing tasks (eg, grocery shopping, cooking, cleaning, transport, and education) with questions adapted from Musick et al [75].

#### Intervention Group and Exposure/Adherence

The intervention group will be assessed based on randomization as a binary variable (intervention vs control). Exposure/adherence to the mHealth intervention will be measured with app-analytics data collected with the platform used to deliver the intervention (ie, Pathverse). Pathverse is a no-code app builder platform that supports mHealth research [76,77], making it easy for researchers to create engaging interventions with preprogrammed features (eg, goal setting, monitoring, feedback) that are known to support behavior change [54]. As Pathverse was developed for research, it collects extensive app analytics data, which can then be examined to assess how many and which components of the intervention the users engaged with. Using these data, adherence will be operationalized as the number of modules completed, self-monitoring tools completed, and goals set and completed.

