**Methods:**

This randomized controlled trial will recruit 118 two-parent families (ie, families with 2 caregivers participating in the trial) from childcare centers across British Columbia, Canada. To promote inclusivity, one-parent families (ie, only one parent participating) will also be eligible but will not count toward the target sample size for recruitment purposes. Eligibility criteria include at least one parent having primary custody of a child aged 2.5-6 years, both parents being fluent in English, and each caregiver owning a smartphone device. In addition, children must not have severe limitations that prevent adherence to general nutritional and 24-hour Movement Guidelines, nor can they be undergoing weight management treatment. After baseline data collection, families will be randomized into either the intervention group, which will receive immediate access to the app, or a waitlist control group, which will gain access to the app after the follow-up assessment, approximately 2 months later. Baseline and follow-up assessments will collect data on food, physical activity, and media parenting practices, coparenting agreement, and child eating, active play, and screen time behaviors. To analyze the data while accounting for its nested structure, multilevel mixed-effects models, integrating intention-to-treat principles and imputation techniques when deemed necessary, will be used. Sensitivity dose-response analyses will assess the extent to which differential adherence/exposure to the intervention influences the study’s outcomes.

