### Analyses

Descriptive statistics will be used to summarize the distribution of the data. Baseline comparisons between groups will be conducted using the Student *t* tests or chi-square tests, as appropriate, for continuous and categorical demographics, primary, and secondary outcomes. These comparisons will assess the extent to which differences remain between groups at baseline despite randomization. To evaluate the effect of the intervention, intention-to-treat multilevel mixed-effects models will be used. These models will be linear, ordered, or logistic, depending on the characteristics of the data and whether transformations are required. The models will examine the effects of the intervention on each key primary and secondary outcome, incorporating an interaction term between time point (baseline or follow-up) and randomization group (intervention or control). These multilevel analyses will account for the nested structure of the sample and the longitudinal nature of the data, with parents nested within families and repeated measures over time. Individual- and family-level covariates will be included in the models as appropriate. Secondary analyses will assess whether changes in parenting and coparenting practices, and the interaction between these two, predict changes in child health behaviors using multilevel and structural equation modeling. Additionally, dose-response sensitivity analyses with mixed-effect models will evaluate the relationship between the level of exposure/adherence to the intervention (measured via app analytics) and the magnitude of changes in parenting and coparenting practices and child health behaviors. If deemed necessary, imputation techniques will be applied to address missing data. In such a case, the specific imputation method (eg, multivariate multiple imputation, chained equations) will be selected based on variable types and patterns of missingness detected in the data.

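### The adherence dose counts completed goals, many of which are the practices the survey appears to score, so the dose-response slope can partly reflect enactment on both sides

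*Protocol article*

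**What the plan says.** Protocol article, Intervention Group and Exposure/Adherence: exposure or adherence is taken from app analytics, and "adherence will be operationalized as the number of modules completed, self-monitoring tools completed, and goals set and completed". The article does not say whether these counts are summed or modelled one by one, or how the app records a goal as completed.

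Analyses: the dose-response sensitivity analyses use mixed-effects models to study "the relationship between the level of exposure/adherence to the intervention (measured via app analytics) and the magnitude of changes in parenting and coparenting practices". Child health behaviours are covered as well. The Methods part of the Abstract says that they will assess "the extent to which differential adherence/exposure to the intervention influences the study’s outcomes".

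The module descriptions list the goals the app recommends. Module 4: "To coparticipate in active play; eat a healthy plate in front of the child; or have family meals". Module 5 includes "limit treats and sugary drinks or screen time". Module 8 includes "praise the coparent for using practices they have agreed on".

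Primary Outcomes: parenting practices are scored by survey, and "Additional items on food, physical activity, and media parenting practices were developed for this study to align with the intervention content".

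**The concern.** Three of the four counts (modules, self-monitoring tools, goals set) describe engagement with the app. The fourth, goals completed, is different in kind. Where the goal is to do a target practice, completing it means that the practice took place. The follow-up survey then asks about practices of that sort, and the analysis relates the two.

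This is not only confounding by motivation. Adjusting for baseline characteristics would not remove it, because enactment is a component of the dose variable itself. A caregiver who changed a practice for any reason and recorded the goal as done has a higher dose and a larger change. What is at stake is how a favourable slope is read: it could be reported as the influence of more exposure when part of it shows only that caregivers who did the practices also recorded doing them.

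**Working it through.** **Does the overlap exist in the text?** Goals set against outcomes:

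| Goal recommended in the app | Outcome in the survey | Match |
|---|---|---|
| Module 7: have the child take part in easy meal-preparation jobs | Primary Outcomes, example of an adapted item: how often the parent has the child do such jobs | Nearly the same behaviour |
| Module 5: "limit treats and sugary drinks or screen time" | Food and media parenting practices (primary); child treat and sugary-drink days and days above one hour of screens (secondary) | Close |
| Module 4: "To coparticipate in active play; eat a healthy plate in front of the child; or have family meals" | Food and activity parenting practices, with extra items aligned to the content | Likely; items not shown |
| Module 8: talk through aims and approaches for the child with the coparent; "praise the coparent for using practices they have agreed on" | Coparenting agreement on expectations, goals and approaches | Related for the first goal, looser for the second |
| Module 3: look for a sport or dance class | No evident item | Weak; a one-off action |

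The overlap is real but partial. It is overlap of construct: the dose is an app count and the outcome is change on a separate survey.

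**How large could it be?** The article gives no figure for this analysis. Its sample size concerns the between-group comparison and reproduces: 2(1.960 + 0.842)² × (0.8/0.5)² = 40.2, so 41 per group; 82/0.7 = 117.1, so 118. It does not bear on this point. The rest is an illustration on stated assumptions.

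*Inputs from the article.* Results: 121 two-parent and 62 one-parent families, so 2 × 121 + 62 = 304 caregivers in 183 families. Randomization: 1:1. Sample Size: 30% attrition. Taking all enrolled families as randomised and evenly split, the intervention arm has 304/2 × 0.7 ≈ 106 caregivers, or 183/2 × 0.7 ≈ 64 families.

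*Assumptions.* App use has no effect on change. Each count is standardised, with half its variance from shared app use and half its own. For completed goals the own half is enactment, which correlates r = 0.3 or 0.5 with reported change. Observations are treated as independent.

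*Formulas.*
- Sum of four counts: variance = 16 × 0.5 + 4 × 0.5 = 10; covariance with change = √0.5 × r; correlation ρ = 0.7071r/√10 = 0.2236r.
- Completed goals alone: ρ = 0.7071r.
- Sum without completed goals: ρ = 0, so the 5% follows by construction.
- Chance of p < 0.05: Φ(z − 1.96) + Φ(−z − 1.96), with z = atanh(ρ) × √(n − 3).

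| Dose | r | ρ | n = 106: z, chance | n = 64: z, chance |
|---|---|---|---|---|
| Four-count sum | 0.3 | 0.067 | 0.68, 10% | 0.52, 8% |
| Four-count sum | 0.5 | 0.112 | 1.14, 21% | 0.88, 14% |
| Completed goals alone | 0.3 | 0.212 | 2.19, 59% | 1.68, 39% |
| Completed goals alone | 0.5 | 0.354 | 3.75, 96% | 2.89, 82% |
| Without completed goals | either | 0 | 5% | 5% |

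Simulation under the same set-up agrees to within about two percentage points.

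*A second set of assumptions.* With 59 units (118/2) and completed goals itself correlating 0.2, 0.3 or 0.5 with change, the simulated chance for the four-count sum is about 7%, 11% and 24% if the counts share a correlation of 0.5, and about 12%, 20% and 49% if they are otherwise uncorrelated. Without completed goals it stays at about 5%. The size moves with the assumptions; the source of the excess does not.

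**The case against.** The article names adherence alongside exposure throughout, and acting on goals set in the app is a normal part of adhering to a programme built on goal-setting. A measure that includes goal completion is a legitimate description of adherence. The Analyses section itself speaks only of a relationship. These points stand. They do not make the mixed measure a good regressor for change in the same practices, and the Abstract's wording goes further than the Analyses section's.

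A reader might infer stronger things, which the documents do not support:

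- *That the goals are the outcomes.* The full item list and the way completion is logged are not shown, some goals are one-off actions, and a caregiver who already had family meals can complete that goal with no change in score.
- *That a false dose-response is nearly certain.* The 59% and 96% apply only if completed goals is used alone as the dose. It is one of four counts, and a condensed article may leave their combination to the analysis plan.
- *That every outcome is affected.* Eating-behaviour scales such as food fussiness or satiety responsiveness are not themselves enacted by completing a parent's goal.
- *That app use after follow-up contaminates the dose.* The article says when access begins in each arm, not that intervention-arm access continues after follow-up.

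**Conclusion.** The point holds in a limited form. By counting completed goals in the dose, the plan lets enactment enter both sides of the dose-response analysis for parenting and coparenting outcomes, and for child outcomes that goals target directly (treats, sugary drinks, screen time). A slope in the favourable direction could arise partly for that reason even if more app use did nothing.

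The size cannot be established from the article. The 10% to 21% for a pooled index (8% to 14% per family), against 5%, rests on the assumed correlations of 0.3 to 0.5 and equal loadings, neither of which has a source in the document. If the counts are modelled separately, the problem is confined to the completed-goals model, where it is larger. Only this sensitivity analysis is affected; the randomised intention-to-treat comparison and the sample size are not. It is worth correcting because the correction is cheap, not because the trial's main conclusion depends on it.

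**What to change.** 1. Define the dose from app engagement: completed modules, completed self-monitoring tools and, if wanted, goals set.
2. Report completed goals separately as enactment, an intermediate measure between exposure and outcome.
3. Describe the relation of completed goals to the outcomes as an association, not as the influence of exposure.

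This takes a sentence or two in the analysis plan and a recoded variable from app analytics that the plan already collects. No information is lost, since completed goals is still reported. The downside is that the dose score loses one component and may vary less between caregivers.
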